## Background

### Literature search and review

In preparation for this study, a systemised review of the literature was performed on preoperative and postoperative falls.^3^ This review showed that a limited number of studies on postoperative falls have been conducted, and the few that have been performed mostly study orthopaedic and elderly populations. While one study characterised postoperative falls in all surgery types, it was limited by its retrospective design, inpatient time period and exclusively male population.^4^ Another study suggested that most postoperative falls may be surgery related, especially in the first weeks following surgery. However, it only tracked falls that resulted in hospital care, and its follow-up period was limited to 90 days.^5^

Regarding the second aim of predicting postoperative outcomes, our systemised review identified just one paper that studied the association between preoperative falls and postoperative complications and readmission.^6^ However, the sample size was small (235), and the population included only men over 65 undergoing cardiac or colorectal surgery at a Veterans Affairs hospital. Using Medical Subject Heading (MeSH) terms of ‘accidental falls’, ‘postoperative period’ and each outcome, a thorough PubMed search was also performed to identify other relevant papers linking falls, surgery and each outcome of interest. This search showed that in non-surgical patients, falls are associated with greater functional dependence.^7^
^8^ In addition, preoperative frailty and geriatric syndromes, which are linked to falls, are associated with postoperative complications^9–14^ and readmission.^15^
^16^ Together, these findings suggest that falls before surgery may presage worse surgical outcomes. However, replication in a larger study is needed.

An additional literature search was performed to identify important confounders for each proposed outcome. Searches consisted of PubMed MeSH for each outcome, along with the MeSH, ‘Risk Factors’, in order to generate a thorough search. Variables that were strongly associated with the outcomes and that would be available to clinicians during preoperative assessment were included as confounders. In addition to confounders from the literature, our previous study on preoperative falls^17^ guided selection of confounders for postoperative falls. That is, variables with ORs of 1.5 or higher were included.

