## Specific aims

*Aim 1*: Describe characteristics of postoperative falls in an unselected surgical population, including their rate, timing, associated injuries and risk factors.

We hypothesise that the occurrence, injuries and risk factors of postoperative falls will be similar to those of preoperative falls, and the rate of postoperative falls will decline from 30-days after surgery to 1 year after surgery.

*Aim 2a*: Determine whether a preoperative history of falls serves as a useful tool for predicting falls in the 30 days (primary outcome) and 1 year following surgery of all types.

*Aim 2b*: Determine whether a preoperative history of falls predicts patient-centred outcomes including functionality and quality of life at 30 days and 1 year after surgery (secondary outcomes).

*Aim 2c*: Replicate findings that a preoperative history of falls predicts in-hospital surgical complications and readmission at 30 days (secondary outcomes).

We hypothesise that a history of preoperative falls will predict poor postsurgical outcomes, including postoperative falls, functional dependence, poor quality of life, in-hospital complications and readmission.

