### Analysis

To begin analysis, we will perform descriptive statistics of all variables used in the analysis, using means, SDs and Student's t-tests for normal, continuous variables; medians, IQRs and Mann-Whitney tests for non-parametric, continuous variables; and proportions and χ^2^ tests for categorical variables. We will explore and report differences between patients with follow-up surveys at 30-days compared with non-responders.^26^ Among patients included in the analysis, we will also explore and report differences between those with complete records versus those with missing data. For variables with missing data, we will perform multiple imputation where appropriate.

Our first aim is to describe the characteristics of postoperative falls in an unselected surgical population, such as their occurrence, timing, injuries and risk factors. To achieve that goal, we plan to perform the following analyses:
Descriptive statistics:
Per cent who fell while still in the hospital;Number of falls (0, 1, 2, 3+) and fall rate in the 30 days and 1-year following surgery;Fall rate and per cent who fell by surgery type (10 surgery departments);Injuries from falls in the 30 days following surgery;Injuries from falls in the 1 year following surgery.▸χ^2^:
Proportion with any injury, comparing preoperative falls to postoperative falls at 30 days and 1 year;Proportion with severe injury, comparing preoperative falls to postoperative falls at 30 days and 1 year.Risk factors: see results from logistic regression model in Aims 2a–c.

As a subaim of Aim 1, we also plan to explore the rate of falls in the short-term versus long-term postoperative periods. To accomplish this, we will calculate the rate of falls per 100 person-years in the Behavioral Risk Factor Surveillance System (BRFSS) system, which serves as the control rate of falling in the general population of adults in the USA. We will then convert the 30-day, 6-month and 1-year fall rates from the SATISFY-SOS population into falls/(100 person-years) using the BRFSS distribution. Finally, we will compare the observed rate of falling to the general population's rate of falling at 1 month and 1 year (Student's t-test) to estimate how the rate of falls changes after surgery.

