Aim 2 explores whether a preoperative history of falls serves as a useful tool for predicting surgical outcomes. First, we will calculate a crude dose–response relationship between the number of falls at baseline (0, 1, 2, 3+) and each outcome (postoperative falls, postoperative functional dependence, postoperative quality of life, in-hospital complications and 30-day readmission). For comparison, we will also calculate the crude dose–response relationship for a falls and injuries composite scale.^27^ We will examine the bivariate relationship between preoperative falls and each complication subcategory (heart/stroke, lung, blood clots, kidney/intestine, nerve injury, infection, delirium or other) using χ^2^ tests for the purpose of hypothesis generation.

To assess the relationship after controlling for important confounders, we will use logistic regression (categorical outcomes) and linear regression (continuous outcomes). Specifically, we will use forced entry of all prespecified variables. We will check all models for linearity of logit, multicollinearity, influential cases, conformity to linear gradients and goodness of fit. Since the number of possible interaction terms is large (between 45 and 91 per model), including all of them creates an unacceptably large risk of type I error. Therefore, our statistical consultant ([name]) recommended selecting only 10% of the most clinically relevant interaction terms. Using a combination of prior research and clinical judgement, two investigators ([name] and [name]) selected the 10% most clinically relevant interaction terms for each model. The online supplementary material contains these prespecified interaction terms. Non-significant interaction terms (p>0.01) will be removed from the model.

10.1136/bmjopen-2016-011570.supp8Supplementary data

Each model will include the following demographic and explanatory variables: age, sex, race (white vs non-white), BMI, preoperative falls history (0, 1, 2, 3+), Charlson Comorbidity Index (≥3 vs <3), American Society of Anesthesiology (ASA) physical status (≥3 vs <3) and procedural cardiac risk. On the basis of a careful literature search of each outcome variable (see the Literature search and review section), we selected confounding variables that are both routinely collected and known at the time of surgery planning. Outcome variables and their corresponding outcome-specific confounders are listed below.

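### The Aim 1 hypothesis of similar risk factors before and after surgery can be neither supported nor refuted by the borrowed Aim 2a model, which adjusts for preoperative falls

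*Protocol article*

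**What the plan says.** **The hypothesis.** Under Specific aims, Aim 1 lists risk factors among the characteristics of postoperative falls to be described, and adds: "We hypothesise that the occurrence, injuries and risk factors of postoperative falls will be similar to those of preoperative falls".

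**The analysis assigned to it.** In the Analysis section, the Aim 1 list gives risk factors no analysis of their own: "Risk factors: see results from logistic regression model in Aims 2a–c". Falls are the outcome only in the Aim 2a model. The pre- versus postoperative χ² comparisons in the same list concern injuries (any, severe) and nothing else.

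**How the Aim 2a model is built.** Every Aim 2 model contains age, sex, race, BMI, preoperative fall history in four levels, Charlson index, ASA status and procedural cardiac risk. The falls model adds physical activity, altered elimination, mobility abnormality, dizziness/vertigo and depression. On entry, "we will use forced entry of all prespecified variables". On timing, "we selected confounding variables that are both routinely collected and known at the time of surgery planning". Literature search and review says that the falls covariates came from a literature search and, in addition, from the team's earlier study of preoperative falls, from which "variables with ORs of 1.5 or higher were included".

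**The concern.** The Aim 2a model is designed to isolate the effect of fall history, and adjusting for fall history is what that aim needs. Aim 1 asks two other questions: which patients fall after surgery, and whether they have the same characteristics as those who fell before it.

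With preoperative falls in the model, the OR for mobility, dizziness or depression measures only the risk not already expressed as earlier falls. A model with preoperative falls as its outcome cannot carry that term, so the two sets of ORs answer different questions. The candidate list was also partly drawn from one of the two sets being compared, and no analysis puts the sets side by side.

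At stake is the interpretation of a stated hypothesis. The Justification section says that knowledge of risk factors should help clinicians to design preventive interventions. Readers could take weak adjusted ORs as evidence that postoperative falls have different causes, or take overlap with a pre-screened list as evidence that they have the same ones.

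**Working it through.** **1. The plan's own figure for this model.** Sample size calculations: 13 predictors × 10 events ÷ 0.10 event rate = 1300 patients. The count of 13 is confirmed as 8 common plus 5 falls-specific variables. About 1500 respondents completed V.3 of the 30-day survey, the version used for postoperative falls. That gives 1500 × 0.10 = 150 events, or 150/13 = 11.5 per variable.

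**2. Does adjusting for fall history matter when a factor acts equally in both periods?** From the protocol: 26% with preoperative falls and 10% with 30-day falls. Assumed, not in the document: factor prevalence 20%, the same conditional OR in both periods, and a shared normal latent frailty with the SD shown (one million simulated patients per row).

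| True OR | Frailty SD | OR, preoperative falls | OR, postoperative, no fall history | OR, postoperative, adjusted |
|---|---|---|---|---|
| 2 | 0.5 | 1.92 | 1.96 | 1.90 |
| 2 | 1.0 | 1.78 | 1.86 | 1.70 |
| 2 | 1.5 | 1.67 | 1.76 | 1.53 |
| 3 | 0.5 | 2.84 | 2.92 | 2.77 |
| 3 | 1.0 | 2.51 | 2.69 | 2.32 |
| 3 | 1.5 | 2.23 | 2.41 | 1.93 |

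Adjustment lowers the postoperative OR by 3% (1.90/1.96) to 20% (1.93/2.41). Against the preoperative OR, the adjusted value lies 1% (1.90/1.92) to 13% (1.93/2.23) below, and the unadjusted value 2% (1.96/1.92) to 8% (2.41/2.23) above. A separate simulation with 25% prevalence, true OR 2.5 and SD 1 gave 2.18, 2.27 and 2.01 in the same order.

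**3. A factor that acts only through earlier falls.** With an OR of 1.5 to 3 for preoperative falls, and an OR of 2 to 4 from preoperative to postoperative falls, the OR for postoperative falls is 1.07 to 1.43 unadjusted and about 1.0 adjusted. In the planned model such a factor disappears, although patients who have it do fall more often after surgery.

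**4. Precision.** For a factor of 20% prevalence near the null, SE of the log OR = √(1/30 + 1/120 + 1/270 + 1/1080) = 0.215. The 99% CI spans a factor of exp(2.576 × 0.215) = 1.74 each way. For preoperative falls, 0.26 × 1500 = 390 events give √(1/78 + 1/312 + 1/222 + 1/888) = 0.147, a factor of 1.46.

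**5. What can enter the falls model.** Surgery type and the in-hospital complications are collected (Table 1), but neither is in it. Procedural cardiac risk is.

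**The case against.** Several counter-arguments have force.

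- **Aim 1 is largely descriptive.** Risk beyond fall history is a legitimate question, and restricting covariates to preoperative ones is deliberate and suits preoperative decision-making. This stands as a defence of the Aim 2a model. It does not supply the comparison that the Aim 1 hypothesis states.
- **The shift is modest.** In the table it reaches the protocol's 20% minimum important difference for ORs only in the strongest case (2.41 to 1.93), and the confidence intervals are wider than the shift. This stands too: the case rests on what the ORs mean, not on a large bias.
- **The earlier study of preoperative falls could be the comparator, and an article condenses.** Possibly, but ORs from a model of preoperative falls are not adjusted for preoperative falls, so the mismatch remains. The point also does not rest on silence: the article itself assigns the risk-factor question to the Aim 2 models.

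A reader might go further and infer that similarity is built in, so that the hypothesis cannot fail. The documents do not support that. Adjusting for fall history pushes towards dissimilarity. The screened list fixes which factors can appear, not their ORs, and under forced entry any of them may come out null or reversed. The earlier study was also only one source beside the literature search. Nor is everything surgical excluded: procedural cardiac risk is in every model, Aim 1 describes fall rates by surgery type and in-hospital falls, and the readmission model contains in-hospital complications.

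**Conclusion.** The concern holds in a limited form. The hypothesis that risk factors are similar has no analysis able to support or refute it. The only falls model gives ORs beyond fall history, from a restricted and partly pre-screened list, with nothing comparable for preoperative falls. This follows from the text alone.

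The size of the distortion depends on assumptions that the protocol does not give. In the simulated cases where a factor acts equally in both periods, attenuation ran from 3% to 20% of the OR; a factor acting only through earlier falls vanished. Severity is low to moderate, because the primary analysis and the rest of Aim 2a are untouched.

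**What to change.** Keep Aim 2a as written. For Aim 1, prespecify two further models in the same V.3 respondents:

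- **(a)** the 30-day falls model without preoperative falls: 12 variables, about 150/12 = 12.5 events per variable;
- **(b)** the same 12 covariates fitted to preoperative falls (any versus none): about 390 events, 390/12 = 32.5 per variable.

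Report the two sets of ORs with 99% CIs side by side. If this is not wanted, reword the risk-factor part of the hypothesis as descriptive. Associations of 30-day falls with in-hospital complications are optional and descriptive only: both come from the same survey, so their order in time is unknown.

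The cost is two extra models from data already requested. Precision at about 150 postoperative events is limited, so the comparison can show large differences but cannot establish equivalence. The covariates in (b) are recorded after the six-month recall period, so those ORs are cross-sectional. Even with fall history removed, the two sets need not agree exactly (2% to 8% apart in the table). The change should be made before analysis starts, because the protocol classes later additions as post hoc.

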## Statistical considerations

### Sample size calculations

The required sample size is calculated based on the primary outcome, which is a fall within 30 days of surgery. Appropriate logistic regression models contain at least 10 ‘events’ per predictor variable.^20^ Since our prespecified model for postoperative falls includes 13 dependent variables (see the Analysis section), a sample with at least 130 events is required. In our population, preliminary work shows that ∼10% of patients report falling in the month following surgery. Thus, the minimum sample size needed for this study is 1300 patients.

Currently, our database contains over 9000 complete records (ie, baseline and 30-day survey) after the 16 January 2014 start date. To meet statistical assumptions of independent observations, we estimate that ∼600 records from patients with at least one previous entry in the data set will be excluded. We estimate that an additional 600 records will be excluded due to inappropriate time intervals (baseline survey to surgery <0 or >59 days; surgery to 30-day survey <20 or >120 days; or surgery to 1-year survey <275 or >455 days). Thus, our final sample size will be ∼7800.

Within this final sample, two versions of the 30-day (V.2 and V.3) and 1-year surveys (V.1 and V.2) were administered. Only V.3 of the 30-day survey and V.2 of the 1-year survey contain a validated falls question, as recommended by the Prevention of Falls Network Europe consensus group.^21^ The difference in question phrasing caused statistically significant differences in the percentage of patients reporting postoperative falls (5.5% vs 10% at 30 days and 18% vs 28% at 1-year, p<0.001). Out of the available records, about 20% (1500) completed V.3 of the 30-day survey, which is more than the 1300 required for the primary outcome. Thus, to maximise outcome validity, only these versions will be used for postoperative falls. In contrast, the readmission question contained only minor differences (‘Were you readmitted to the hospital?’ for V.2 vs ‘Check all that apply […] admitted to a hospital’ for V.3). The percentage reporting readmission was similar between surveys (5.2% vs 5.7%, p=0.416), so the results from both versions will be combined. The remaining outcomes were identical and will use all available data from both versions of the 30-day and 1-year surveys.

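### The Aim 1 test of postoperative falls against BRFSS does not establish that the two surveys measure falls alike, so an instrument difference could be read as a change after surgery

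*Protocol article*

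**What the plan says.** Under Analysis, the Aim 1 subaim names BRFSS as the comparator; its rate "serves as the control rate of falling in the general population of adults in the USA". The cohort's 30-day, 6-month and 1-year rates are converted "into falls/(100 person-years) using the BRFSS distribution". Then "we will compare the observed rate of falling to the general population's rate of falling at 1 month and 1 year" by Student's t-test, and the stated purpose is "to estimate how the rate of falls changes after surgery".

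Under Sample size calculations, the protocol reports on its own survey versions: "The difference in question phrasing caused statistically significant differences in the percentage of patients reporting postoperative falls (5.5% vs 10% at 30 days", with 18% against 28% at 1 year and p<0.001 for the differences. It adds that "Only V.3 of the 30-day survey and V.2 of the 1-year survey contain a validated falls question" and concludes: "Thus, to maximise outcome validity, only these versions will be used for postoperative falls". At 30 days this leaves about 1500 of about 7800 records.

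Table 1 gives preoperative and postoperative falls the same standardised-tool reference. The Limitations section discusses the two survey versions but does not mention BRFSS.

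**The concern.** The protocol will not combine two versions of its own follow-up survey for falls because, in its judgement, phrasing moved the answers materially. It then compares the validated version with a national survey and interprets the gap as what surgery does to fall rates. No section says that the BRFSS item matches the validated question, and no allowance is made for a difference in wording, mode or recall. Conversion to person-years does not change the chance that a person who fell reports it.

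Recall is a further mismatch that does not depend on the BRFSS wording. One follow-up item covers about a month and the other a year, so one BRFSS rate cannot share its recall period with both.

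What is at stake is attribution. If reporting differs between the instruments, a test of equal rates can reject although the underlying fall rates are equal. The result could then be published as an effect of surgery, or could hide one. Standardising for age and sex would not remove this.

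**Working it through.** **Inputs.** From Sample size calculations: 5.5% against 10% at 30 days, 18% against 28% at 1 year, p<0.001, about 1500 records with the validated 30-day question, final sample about 7800. From Analysis: significance threshold α=0.01, taken as two-sided. Not in the document: the BRFSS question, its recall window and rate, and the number with the validated 1-year question.

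**Reproducing the protocol's figure.** At 30 days the non-validated version has 7800 − 1500 = 6300 records. The pooled proportion is (0.055×6300 + 0.10×1500)/7800 = 0.0637, and z = 0.045/√(0.0637×0.9363×(1/6300 + 1/1500)) = 6.4, p ≈ 1.4×10⁻¹⁰. This agrees with p<0.001. At 1 year the group sizes are not stated. With assumed equal groups of 500, p = 0.00017; with 300, p = 0.0036. The stated p<0.001 is therefore consistent with groups of about 500 or more.

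**Size of the version effect.**
- Proportion who fell: 10/5.5 = 1.82 at 30 days; 28/18 = 1.56 at 1 year.
- Person-time, assuming a constant rate, −100·ln(1−p)/t: at 30 days 69 against 128 per 100 person-years (ratio 1.86); at 1 year 19.8 against 32.9 (ratio 1.66).

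**What an instrument gap would do to the test.** Assume no true difference, the BRFSS rate fixed, and a one-sample test of a proportion with normal approximation. Let p_hi be the percentage on the validated question (10% or 28%), and p_lo = p_hi/ratio the percentage that the same true risk would produce on the other instrument. Then

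P(reject) = Φ((p_hi − p_lo − 2.576·√(p_lo(1−p_lo)/n)) / √(p_hi(1−p_hi)/n)).

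Worked case, ratio 1.20, 10% endpoint, n=1500: p_lo = 0.0833; null SE = 0.00714; 2.576×0.00714 = 0.0184; SE under p_hi = 0.00775; (0.0167 − 0.0184)/0.00775 = −0.22; Φ = 0.41.

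| Assumed ratio | 10% endpoint | 28% endpoint |
|---|---|---|
| 1.05 | 3% | 8% |
| 1.10 | 10% | 38% |
| 1.20 | 41% | 95% |
| 1.30 | 76% | >99% |

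The nominal level is 1%. The n of 1500 comes from the protocol at 30 days and is assumed at 1 year. The calculation ignores the distributional step in the person-year conversion, so it illustrates sensitivity and does not model the planned t-test exactly.

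**The case against.** The strongest reply is that the mismatch is not shown. The BRFSS item is not quoted, and an article need not reproduce it. The subaim is exploratory, and the Aim 1 hypotheses concern similarity to preoperative falls and a decline from 30 days to 1 year, not an excess over the general population. In the 30-day against 1-year contrast the validated question is used at both times and a common BRFSS denominator cancels. The plan also converts a 6-month rate. Since there is no 6-month survey and the exposure window is the 6 months before surgery, this is most plausibly the preoperative rate, measured with the same tool.

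Most of this stands, and it limits the point. It does not remove it, because the planned test is against BRFSS and its stated purpose is to estimate change after surgery.

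Three stronger readings are tempting, and the document does not support them:
- **That false rejection is nearly certain.** With the full version gap the formula gives over 99% at 30 days (n=1500), and 95% at n=300 or over 99% at n=500 at 1 year. This requires BRFSS to report falls exactly as the discarded versions do, which nothing in the document says.
- **That the bias would appear as an excess of falls after surgery.** The direction is unknown.
- **That wording alone has been shown to cause the 1.6- to 1.8-fold gap.** That is the protocol's own attribution. Random allocation of versions is not described, so other differences between the groups may contribute.

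**Conclusion.** The concern holds as a problem of comparability. The protocol tests the validated-question rates against an external rate and reads the difference as a change after surgery, without establishing that the two surveys measure falls alike. Its own attribution of a 1.56- to 1.82-fold gap to phrasing shows that it regards such differences as material.

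The size and direction of any bias cannot be derived from the document. Under the stated assumptions, a 5% instrument difference raises false rejection from the nominal 1% to about 3% (10% endpoint) or 8% (28% endpoint), and a 20% difference raises it to about 41% or 95%.

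The point is confined to an exploratory subaim. The primary outcome, its model and its sample size do not depend on BRFSS, and the 30-day against 1-year contrast within the cohort is not materially affected. The change is worth making before analysis but is not critical to the study's main conclusions.

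**What to change.** In the Aim 1 subaim under Analysis:

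1. Replace the t-test verdict against BRFSS with rate ratios and 99% CIs, labelled as a descriptive external benchmark.
2. Report beside it the 30-day and 1-year rates against the cohort's own preoperative 6-month rate, in the same person-time units, and base the statement on how falls change after surgery on this comparison. Table 1 lists both under the same standardised tool. The recall windows still differ, and the text should say so.
3. As a sensitivity analysis, repeat the BRFSS ratio for the proportion who fell under the non-validated version. The proportion is needed because Table 1 records the 30-day V.2 falls item as binary, so fall counts are not available. Do not attribute to surgery a departure from BRFSS, in either direction, that is no larger than the study's own version effect: a ratio between 0.55 and 1.82 at 30 days (5.5/10 and 10/5.5), or between 0.64 and 1.56 at 1 year (18/28 and 28/18). State that the two in-house versions need not bracket BRFSS.

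Under Sample size calculations, add that the non-validated versions are kept for this sensitivity analysis only, as an exception to the rule that "only these versions will be used for postoperative falls".

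The cost is some protocol wording and additional tabulation from data already collected. The statement about the cohort against the general population becomes weaker and may be inconclusive.

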**Methods and analysis:**

To achieve these goals, we study adult patients who underwent elective surgery at our academic medical centre and were recruited to participate in a prospective, survey-based cohort study called Systematic Assessment and Targeted Improvement of Services Following Yearlong Surgical Outcomes Surveys (SATISFY-SOS) (NCT02032030). Patients who reported falling in the 6 months prior to surgery will be considered ‘exposed.’ The primary outcome of interest is postoperative falls within 30 days of surgery. Secondary outcomes include postoperative functional dependence, quality of life (both physical and mental), in-hospital complications and readmission. Regression models will permit controlling for important confounders.

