Comparing patients who reported falling preoperatively with those who did not, a sample size of 1500 has 80% power to detect a 58% increase in postoperative falls within 30 days. The estimated percentage of patients who experience functional decline in the month following surgery is 20%.^22^ Our own data suggest that the SD for quality of life is 11, 28% of patients experience in-hospital complications, and 5.5% of patients are readmitted within 30 days. Thus, a sample size of 7800 patients has 80% power to detect a 15% increase in functional decline after surgery, a 0.8 point difference in physical and mental qualities of life, a 12% increase in in-hospital complications, and a 34% increase in 30-day readmission. All of the above calculations used two tails, α=0.05 and a baseline fall proportion of 26%.^17^

The minimum important difference will be a 20% difference in proportions or ORs.^23^ From the calculations above, the detectable effect sizes for falls and readmission are larger than this prespecified threshold. However, the results of interest are the ORs from regression models rather than crude bivariate analysis. For quality of life estimates, the minimum important difference will be five points.^24^
^25^

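### The Aim 1 subaim measures the change in fall rate after surgery only against US adults in general; no listed analysis compares it with the patients' own preoperative falls

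*Protocol article*

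**What the plan says.** The Analysis section describes an exploratory subaim of Aim 1 on short-term and long-term fall rates. It takes the BRFSS rate as reference, "which serves as the control rate of falling in the general population of adults in the USA". It continues: "We will then convert the 30-day, 6-month and 1-year fall rates from the SATISFY-SOS population" into falls per 100 person-years. The last step is to "compare the observed rate of falling to the general population's rate of falling at 1 month and 1 year" by Student's t-test, "to estimate how the rate of falls changes after surgery".

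The Specific aims state the Aim 1 hypothesis in two parts: that the "occurrence, injuries and risk factors of postoperative falls will be similar to those of preoperative falls", and that the postoperative rate declines from 30 days to 1 year.

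The patients' own preoperative falls are the exposure of the study. The abstract says "Patients who reported falling in the 6 months prior to surgery will be considered" exposed. Table 1 records preoperative falls from the baseline survey as 0, 1, 2 or 3+, and cites the same standardised tool for preoperative and postoperative falls.

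The only before-versus-after tests listed under Aim 1 are χ² tests on the proportions with any injury and with severe injury.

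**The concern.** A change after surgery is a difference between two periods in the same patients. A comparison with BRFSS is a difference between two populations. If surgical candidates already fall more often than US adults before their operation, through pain, poor mobility or comorbidity, that excess appears in the postoperative comparison whether or not anything changed.

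The first part of the Aim 1 hypothesis, similar occurrence before and after surgery, therefore has no analysis attached. Aim 2a does not fill the gap. Its logistic model asks whether patients who fell before surgery are more likely to fall afterwards, which is an association between patients and not a comparison of occurrence in the two periods.

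The comparators could also disagree at 1 year: the cohort could lie above the population rate and below its own preoperative rate.

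**Working it through.** The document states no rate or power for this subaim, so there is no figure of its own to reproduce. The check asks how far the choice of comparator could matter on the proportions it does give.

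**Inputs**
- Preoperative: "a baseline fall proportion of 26" per cent (Sample size calculations, cited from earlier work). I read this as a 6-month proportion, which is an assumption.
- Postoperative: "5.5% vs 10% at 30 days and 18% vs 28% at 1-year". The higher figure of each pair belongs to the validated wording, so 10% and 28%.
- General population: not given. Assumed range 10% to 30% of adults falling per year.

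**Step 1. Rates at a constant first-fall hazard,** −ln(1 − p)/t, per 100 person-years:
- before surgery: −ln(0.74)/0.5 = 60.2
- first 30 days: −ln(0.90)/(30/365.25) = 128.3
- 1 year: −ln(0.72)/1 = 32.9

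Ratios to the preoperative rate: 128.3/60.2 = 2.13 and 32.9/60.2 = 0.55. With the linear form p/t the rates are 52.0, 121.8 and 28.0, and the ratios 2.34 and 0.54.

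**Step 2. The planned comparator,** over the assumed range:

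| Adults falling per year | Population rate | Preoperative ratio | 30-day ratio | 1-year ratio |
|---|---|---|---|---|
| 10% | 10.5 | 5.7 | 12.2 | 3.1 |
| 15% | 16.3 | 3.7 | 7.9 | 2.0 |
| 20% | 22.3 | 2.7 | 5.7 | 1.5 |
| 25% | 28.8 | 2.1 | 4.5 | 1.1 |
| 30% | 35.7 | 1.7 | 3.6 | 0.9 |

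On these inputs the cohort already exceeds the population before surgery in every row. The 1-year rate is above the population for any value below 28% per year, while the same-patient ratio is below 1. The 30-day to 1-year ratio is 128.3/32.9 = 3.9 in every row, because the reference cancels.

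**Step 3. Do the same-patient ratios in Step 1 show a real change?** They need not.
- *Repeat fallers.* Let the fall rate be constant over time but vary between patients with a gamma frailty: P(fall by t) = 1 − (1 + v·m·t)^(−1/v). With illustrative values m = 1.83 falls per person-year and v = 6.4:
  - 30 days: 1 − 1.962^(−0.156) = 10%
  - 6 months: 1 − 6.856^(−0.156) = 26%
  - 1 year: 1 − 12.712^(−0.156) = 33%

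  The Step 1 formula turns these into about 128, 60 and 40, with ratios of 2.13 and 0.66, although nothing changed.
- *Recall window.* The Limitations section says the 30-day surveys fall between 20 and 120 days after surgery. If the 10% accumulated over 20, 45, 60 or 120 days, the first ratio becomes 3.2, 1.42, 1.07 or 0.53.

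**Step 4. Overlap.** The 1-year window contains the first 30 days. Naive removal gives (0.3285 − 0.1054)/(335/365) = 0.243, or about 24 per 100 person-years instead of 33. The document does not show that the 10% and 28% come from the same patients, so this too is only indicative. The overlap works against the hypothesised decline and cannot create false support for it.

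**The case against.** The strongest reply has four parts.

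1. **The plan makes no causal claim.** A reader might infer that standing excess risk will be reported as an effect of surgery. The document does not say this; it speaks of how the rate changes and never attributes an excess over BRFSS to the operation. This part of the reply stands in full.
2. **The patients' own rate is probably already there.** No 6-month follow-up survey is described, and the only 6-month window in the document is preoperative. The converted 6-month rate is therefore most likely the preoperative one, and all three cohort rates would stand beside BRFSS on one scale. So it cannot be said that the plan ignores the preoperative rate. It remains true that this rate is unlabelled and that the stated comparison, at 1 month and 1 year, is with the general population only.
3. **The declared short-term versus long-term contrast largely survives.** Both time points use the same reference, as Step 2 shows. This stands.
4. **The patients' own baseline is not clean either.** The condition that led to surgery may raise falls beforehand, and the recall windows differ. This stands as a caveat. It does not make an external population a measure of change.

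**Conclusion.** The point holds in limited form. As written, the subaim cannot show how the cohort's fall rate changed from before surgery, and the hypothesis of similar occurrence has no test, although the data for one are collected. This follows from the text and needs no numerical assumption.

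The size is unknown. A reader might take 2.13 and 0.55 as evidence that falls double and then halve. The documents do not support that. The figures rest on a common constant hazard, an exact 30-day window, and a 26% from earlier work read as a 6-month proportion. Step 3 reproduces the first ratio, and much of the second, with no change at all. The possible reversal of direction at 1 year rests on the same assumptions plus an assumed population rate.

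This is an exploratory subaim of a descriptive aim. The primary outcome, Aim 2 and the sample size are not affected. It is a cheap improvement, not a defect that threatens the study.

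**What to change.** - State what the 6-month rate is: the preoperative rate, or whatever else is meant.
- Prespecify a same-patient comparison of preoperative with 30-day and 1-year falls. Use only the validated survey versions, actual person-time from the survey dates, and a paired or clustered model that respects the 0, 1, 2, 3+ cap, such as an ordinal or censored-count model. An ordinary Poisson or negative binomial model would ignore the cap.
- Keep BRFSS as descriptive context.
- State that the 1-year window includes the first 30 days. Add a sensitivity analysis in patients with both validated surveys where the capped counts allow it; simple subtraction is undefined when the 1-year answer is 3+.
- State the caveats: recall windows of 6 months, 20 to 120 days and about 1 year; preoperative rates possibly raised by the condition treated; and a possibly small overlap. Only about 1500 patients completed the validated 30-day version, and the number who also completed the validated 1-year version is not given.

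The cost is wording and a modest extra analysis with no new data collection. It is best settled before analysis starts, because the plan says that analyses added later will be labelled post hoc and hypothesis-generating.
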